**Appendix III : Severity Criteria implying to start antibiotics after the BAL**

- **Respiratory failure:** at least one of the following criteria: 1) PaO2 / FiO2 < 200 mmHg; 2) score radio >3

- **Cardiovascular failure:** at least one of the following criteria: 1) Systolic Arterial Pressure < 60 mmHg; 2) use of vasopressor or inotropic substances (Dopamine > 5 µg / kg / min) to keep a SAP >90mmHg ; 3) volume expansion >1.5 litres / 24 hours

- **Renal failure:** diuresis <30 ml/h or 0.5 ml/kg/h or 6 H diuresis <200 ml

- **Haematological failure:** at least one of the following criteria: 1) leukocytosis <2 000 / mm3; 2) platelets <40 000 / mm3

- Patient with a prosthetic valve (known or documented)

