**5. Treatment**

**5.1 Intitiating the treatment**

A BAL will be made upon suspicion of nosocomial pneumonia (clinical and radiological criteria defined in Section 4). Patients will be treated either after the BAL bacteriological results, or immediately after the BAL according to the predefined severity criteria (Appendix III). If the antibiotic treatment is started immediately after the BAL, the patient will be included in the study as long as the treatment is not changed after the results of the sensitivity.

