**Appendix IV : Definition of septic shock**

- Systolic blood pressure < 90 mm Hg (or decrease from the usual value by at least 30 mmHg not responding to volume expansion, in the presence of a septic syndrome.

*Baumgartner J.D., Critical Care Medecine 1992 ; 20 (7) : 953-960.*

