**Appendix X : Definition of organ failure ( ODIN )**

Respiratory failure (at least one of the following criteria):

- PaO2 < 60mmHg with FiO2 = 0, 21

- Artificial ventilation

Cardiovascular failure (at least one of the following criteria in the absence of hypovolemia):

- systolic blood pressure <90 mmHg with signs of peripheral hypoperfusion
- use of inotrope or vasopressor to maintain a systolic blood pressure >90 mmHg

Renal failure (at least one of the following criteria in the absence of chronic renal failure):

- serum creatinine >300µmol/l
- diuresis <500 ml/24 hours or 180 ml / 8 h
- need of renal replacement therapy

Neurological failure (at least one of the following criteria):

- score of Glasgow <6 (in the absence of sedation)
- sudden onset of confusion

Hepatic failure (at least one of the following criteria):

- bilirubin >100µmol/l
- phosphatase alkaline (x 3 normal)

Hematological failure (at least one of the following criteria):

- Hematocrit <20%
- leukocytosis <2,000 / mm3
- platelets <40,000 / mm3

*Fagon et coll, Intens.Care Med. 1993 ; 19 : 137-144.*

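### Appendix III's only direct blood-pressure trigger for immediate antibiotics is systolic below 60 mmHg, so a probably small group meeting the protocol's own shock or hypotension definitions would wait for the BAL result

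*Protocol*

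**What the plan says.** Section 5.1 sets the timing of the first dose: "Patients will be treated either after the BAL bacteriological results, or immediately after the BAL according to the predefined severity criteria". The severity criteria are those of Appendix III. A patient started immediately carries a further condition: "the patient will be included in the study as long as the treatment is not changed after the results of the sensitivity".

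Appendix III lists three cardiovascular triggers, any one of which is enough:

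1. "Systolic Arterial Pressure < 60 mmHg";
2. a vasopressor or inotrope (dopamine above 5 µg/kg/min) used to hold systolic pressure above 90 mmHg;
3. volume expansion above 1.5 litres in 24 hours.

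It also has respiratory, renal and haematological triggers, and one for a prosthetic valve.

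Two other appendices define related states:

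- Appendix X (ODIN) opens its entry with "Cardiovascular failure (at least one of the following criteria in the absence of hypovolemia" and gives as its first criterion "systolic blood pressure <90 mmHg with signs of peripheral hypoperfusion".
- Appendix IV defines septic shock as "Systolic blood pressure < 90 mm Hg", or a fall of at least 30 mmHg from the usual value, "not responding to volume expansion, in the presence of a septic syndrome". The bracket in that sentence is never closed; I read the volume and sepsis qualifiers as covering both limbs.

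**The concern.** The list that decides who may not wait uses a lower pressure limit than the lists that decide who is in cardiovascular failure or septic shock. The ODIN score is taken at pre-inclusion, on the day of the BAL. A site could therefore record cardiovascular failure by Appendix X and, on the same day, be sent by section 5.1 down the waiting route for that patient. Section 6 does not exclude patients in shock, so such a patient can be eligible.

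Appendix III is also uneven within itself. A patient held above 90 mmHg on a qualifying vasopressor is treated at once. A patient at 75 mmHg without one, who has had 1.5 litres or less and has no other listed item, waits.

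What is at stake is delayed treatment in a few sick patients, and consistency between appendices. It is not the validity of the comparison between arms.

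**Working it through.** The protocol states no figure that could be reproduced here. The check applies the three sets of criteria to the same patient.

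**Test patient.** No vasopressor, 1.0 litre of volume, PaO2/FiO2 of 250, radiological score 3, normal diuresis, leukocytes and platelets above the Appendix III limits, no prosthetic valve. For Appendix X, hypoperfusion is present and hypovolaemia absent. For Appendix IV, pressure does not respond to volume and there is a septic syndrome; only the 90 mmHg limb is tested.

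| Systolic (mmHg) | Appendix III (start now) | Appendix X hypotension | Appendix IV shock |
| --- | --- | --- | --- |
| 55, 59 | met | met | met |
| 60, 70, 80, 89 | not met | met | met |
| 90 | not met | not met | not met |

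Adding any one of a qualifying vasopressor, more than 1.5 litres, a radiological score above 3, or oliguria meets Appendix III at every pressure tested.

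The gap on the 90 mmHg limit is therefore systolic 60 to 89 mmHg with every other Appendix III item absent. The 30 mmHg limb of Appendix IV, not in the table, can extend it to patients at 90 mmHg or above whose usual pressure is high.

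**Can an eligible patient lack the radiological item?** Appendix I scores four quadrants from 0 to 3, so the range is 0 to 4 × 3 = 12. Section 4.2 requires a rise of 2 points from admission; the Appendix III trigger is a score above 3.

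- Admission 0: 0 + 2 = 2 or 0 + 3 = 3, no trigger.
- Admission 1: 1 + 2 = 3, no trigger.
- Admission 2: 2 + 2 = 4, trigger.

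The item can be absent only if the admission score was 0 or 1. A normal admission film followed by condensation in one quadrant scores 3 and is such a case, so the gap is not empty.

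**How long is the wait?** Section 5.1 gives no duration. Section 4.3, which sets the bacteriological criterion, contains only the quantitative culture, and section 8.2 ties final inclusion to the bacteriological result. Appendix II has plates read at 24 and 48 hours. Waiting for culture is the natural reading, but it is inferred.

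**How many patients?** This cannot be derived. The protocol gives no distribution of blood pressure, fluid volume or radiological score at the time of the BAL.

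**The case against.** **Different purposes.** The three appendices serve to start treatment, to judge failure (section 7.2.1 uses Appendix IV) and to score organ failure. They need not agree, and Appendix III does not simply copy Appendix X. Artificial ventilation alone is respiratory failure in Appendix X, whereas Appendix III asks for PaO2/FiO2 below 200 or a score above 3. Appendix III adds a dopamine floor and a volume trigger. This stands as far as it goes: no error is proved. But the differences do not all point to a stricter list. The leukocyte and platelet limits are identical, and the urine trigger is more sensitive in Appendix III (30 ml/h, against 500 / 24 = about 21 ml/h in Appendix X).

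**Other items catch most of them.** Shock that does not respond to volume usually leads to a vasopressor or more than 1.5 litres, and hypoperfusion often brings oliguria. A patient who reaches such a trigger while waiting then meets Appendix III. This stands, and it is why the point is minor.

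**The text may leave room.** The awaited result might include the Gram stain described in Appendix II; the title of Appendix III can be read as naming who must start, with earlier treatment of others not expressly forbidden; and section 9.3 calls for treatment suited to the patient's state. None of these closes the gap. Section 5.1 does not name the Gram stain as a trigger, it attaches the immediate route to the severity criteria, and section 9.3 concerns intercurrent events under side effects.

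**A stronger inference.** A reader might conclude that 60 is a misprint for 90, since the next item in Appendix III uses 90. The document does not show this; 60 may be deliberate.

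**Conclusion.** The point holds as a cheap improvement of minor severity. Followed literally, section 5.1 makes some patients wait for the BAL result although they meet Appendix IV septic shock or the Appendix X hypotension criterion. The group is probably small; its size is unknown and should not be given a number.

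A reader might also infer that the trial's result is affected. It is not: the timing rule acts before randomisation and in the same way for both arms, so the 8 versus 15 day comparison is not biased.

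The conclusion rests on two readings: that Appendix III is the only gate to immediate treatment, and that the awaited result is the culture. The first is close to the wording of section 5.1; the second is inference.

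**What to change.** In Appendix III, cardiovascular item 1, keep the 60 mmHg trigger unconditional and add two alternatives beside it: systolic pressure below 90 mmHg with peripheral hypoperfusion and no hypovolaemia, or septic shock according to Appendix IV. Nobody who qualifies today is dropped, and the change works whether or not 60 was intended.

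Two simpler edits are worse:

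- Replacing 60 by 90 would start treatment in every patient at 60 to 89 mmHg, with or without hypoperfusion, and would still miss the 30 mmHg limb of Appendix IV.
- Importing the whole Appendix X cardiovascular entry would bring in "use of inotrope or vasopressor to maintain a systolic blood pressure >90 mmHg", which has no dose floor and would override the dopamine limit of 5 µg/kg/min in item 2. That limit should stay as it is.

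The cost is one appendix line and a small operational downside. A few more patients would start before culture and come under the section 5.1 condition that treatment is unchanged after sensitivities. Section 11.2 plans for a 20% loss between pre-inclusion and inclusion (350 × 0.20 = 70 patients, leaving 280). That loss may rise slightly; the document gives no basis for saying by how much.

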**Appendix IV : Definition of septic shock**

- Systolic blood pressure < 90 mm Hg (or decrease from the usual value by at least 30 mmHg not responding to volume expansion, in the presence of a septic syndrome.

*Baumgartner J.D., Critical Care Medecine 1992 ; 20 (7) : 953-960.*

**Appendix V : Sepsis-related Organ Failure Assessment (SOFA)**

**Appendix VI : Complications related to treatment**

- Acute renal failure (2X serum creatinine from the value before treatment):-severe: anuria - conserved diuresis
- Skin complications:-severe: Lyell syndrome – other skin lesions
- Digestive complications:-severe: pseudomembranous colitis – other
- Hematological complications:-severe: anemia, leukopenia, neutropenia, thrombocytopenia grade 3 or 4 (table below)-other ranks
- Allergic complications:-severe: anaphylactic shock – other

Others (hepatitis, enkephalopathy, lung disease)Haematologic toxic acute and subacute ( WHO)

| haematological | grade 0 | grade 1 | grade 2 | grade 3 | grade 4 |
| --- | --- | --- | --- | --- | --- |
| Haemoglobin G/100ml | **11** | **9.5-10.9** | **8.0-9.4** | **6.5-7.9** | **6.5** |
| leucocytes G/L | **4.0** | **3.0-3.9** | **2.0-2.9** | **1.0-1.9** | **1** |
| Neutrophils G/L | **2.0** | **1.5-1.9** | **1.0-1.4** | **0.5-0.9** | **0.5** |
| Platelets G/L | **100** | **75-99** | **50-74** | **25-49** | **25** |
| Haemorrhage | **No** | **purpura** | **small** | **large** | **severe** |

**Appendix VII : Daily follow up sheet**

**Day :**

**Alive**  **Dead**

**ICU** : Yes No

**Transfert** : Ward

Home

**Evolution of the early onset VAP :**

Temp max

Leucocytosis

PaO2 /FIO2

Radiological score

ODIN (Appendix X)

SOFA (Appendix V)

Shock ( Annexe IV ) : Yes No

Surperinfection : Yes No

BAL result:

**Secondary infections :**

***Sites* : -** Bacteremia Yes No Antibiotic sensitivity

- Catheter Yes No

- Urines Yes No

- Other :

**Economic data :**

***Examinations* : -** Ultrasound

- Chest X-Ray

- CT scan

***Equipment :***  - Swan Ganz catheter

- hemodialysis

- hemofiltration

***Treatment :*** *-* Antibiotics

- Other

**Side effects of the treatment** :

Present : Yes No

Relationship with the treatment Yes No

**Appendix VIII : SAPS II**

**Appendix IX : Mc Cabbe Classification**

This classification takes into account the existence of underlying disease and the appreciation of its prognosis in the three months preceding hospitalization and resuscitation. This very simple grouping allows us to distinguish between very different prognosis groups.

- 0: absence of underlying disease or underlying diseases not affecting the vital prognosis
- 1: underlying diseases are affecting the overall prognosis within 5 years
- 2: fatal – death from underlying diseases estimated within 1 year

**Appendix X : Definition of organ failure ( ODIN )**

Respiratory failure (at least one of the following criteria):

- PaO2 < 60mmHg with FiO2 = 0, 21

- Artificial ventilation

Cardiovascular failure (at least one of the following criteria in the absence of hypovolemia):

- systolic blood pressure <90 mmHg with signs of peripheral hypoperfusion
- use of inotrope or vasopressor to maintain a systolic blood pressure >90 mmHg

Renal failure (at least one of the following criteria in the absence of chronic renal failure):

- serum creatinine >300µmol/l
- diuresis <500 ml/24 hours or 180 ml / 8 h
- need of renal replacement therapy

Neurological failure (at least one of the following criteria):

- score of Glasgow <6 (in the absence of sedation)
- sudden onset of confusion

Hepatic failure (at least one of the following criteria):

- bilirubin >100µmol/l
- phosphatase alkaline (x 3 normal)

Hematological failure (at least one of the following criteria):

- Hematocrit <20%
- leukocytosis <2,000 / mm3
- platelets <40,000 / mm3

*Fagon et coll, Intens.Care Med. 1993 ; 19 : 137-144.*

**Appendix XII : Side effects declaration**

Mail to : [name] de réanimation médicale CHU Besançon

[contact]

Centre : Postal Code:

Investigator :

Patient :

Randomization: ARM: Short Long

Treatment : Onset After BAL result

Starting Treatment Date :

Side effects Date :

Description :

Complications :

Relationship with the treatment : Yes No

If Yes which arguments

Treatment : Stop

Pursuit

Adjustment of the dosage

**Appendix XIII : Nosocomial Superinfection definitions**

- Bacteremia: 1 positive blood culture or 2 positive blood cultures if Staphylococcus épidermidis
- catheter: cultures of the tip of the catheter > 10 3 cfu /ml
- Urine : cultures >10 5 cfu / ml and Neutrophils > 10 / field
- Pulmonary: BAL sample culture >10 4 ufc/ml
- Sinusitis: sinus puncture positive
- Surgical wounds: growth of bacteria on local sample

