**4 Diagnosis of early onset nosocomial infection**

The diagnosis of early onset ventilator associated pneumonia is confirmed if all of the following criteria is met:

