**7.4 Non-pulmonary infectious intercurrents events**

Any modification of antibiotics will be preceded by the collection of bacteriological samples deemed necessary. If an intercurrent non-pulmonary Infection is documented, the patient is considered superinfected and remains evaluable at D21 on intention to treat.

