**10.1 Study of nosocomial superinfections**

**Objective:** to evaluate the influence of the duration of antibiotic treatment on the prevalence of fatal pulmonary and extra-pulmonary infections (definitions of nosocomial infections: Appendix XIII).

**Method:** Consideration of all the infectious intercurrents events observed while the patient is in an intensive care unit, for a maximum period of 3 weeks.

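### Appendix XIII defines catheter, lung, sinus and wound superinfection by culture alone, so the section 10.1 comparison mixes colonisation or persistence with infection

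*Protocol*

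**What the plan says.** The first secondary objective (section 3, repeated in section 10.1) asks whether treatment duration influences pulmonary and extra-pulmonary infection. Both places refer to Appendix XIII for the definitions. The method in section 10.1 is "Consideration of all the infectious intercurrents events observed while the patient is in an intensive care unit", for at most three weeks.

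Four lines of Appendix XIII name only a culture result:

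- Catheter: "catheter: cultures of the tip of the catheter > 10 3 cfu /ml"
- Lung: "Pulmonary: BAL sample culture >10 4 ufc/ml"
- Sinus: "Sinusitis: sinus puncture positive"
- Wound: "Surgical wounds: growth of bacteria on local sample"

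The urine line adds a host response: "Urine : cultures >10 5 cfu / ml and Neutrophils > 10 / field". The bacteraemia line has its own safeguard, since it asks for two positive cultures for a common skin organism.

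For the index pneumonia, section 4 states "The diagnosis of early onset ventilator associated pneumonia is confirmed if all of the following criteria is met", and then lists clinical, radiological and BAL criteria. Section 7.3 says that a new BAL documents an intercurrent pulmonary event, and that the patient is superinfected if a different organism is found at significant concentration. For non-pulmonary events, section 7.4 says "Any modification of antibiotics will be preceded by the collection of bacteriological samples deemed necessary".

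**The concern.** A positive catheter tip, sinus puncture, wound swab or BAL can reflect colonisation. Taken as written, four lines of Appendix XIII do not separate that from infection. A second lung infection is held to a looser standard than the first, and persistence of the index organism satisfies the lung line although section 7.3 would not call it superinfection.

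The distinction matters here because section 2.2 names colonisation by multi-resistant bacteria as a possible consequence of longer treatment, separate from infection, and section 10.2 studies the flora in its own right. If the superinfection outcome also picks up colonisation, the two questions run together. The trial is open and the choice of non-pulmonary samples is left to judgement, so the number of cultures taken can differ by arm. At stake is whether a difference in section 10.1, or its absence, can be read as an effect of duration on infection.

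**Working it through.** **1. Site by site**

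| Site | Culture condition | Further condition in Appendix XIII |
| --- | --- | --- |
| Catheter | tip above 10^3 cfu/ml | none |
| Lung | BAL above 10^4 cfu/ml | none (section 7.3: different organism) |
| Sinus | positive puncture | none |
| Wound | any growth | none |
| Urine | above 10^5 cfu/ml | neutrophils above 10 per field |
| Blood | one positive culture | two if *S. epidermidis* |
| Index pneumonia (section 4, for contrast) | BAL above 10^4 cfu/ml | 2 of 3 clinical signs, and a 2-point radiological rise |

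**2. Does another section supply the missing signs?** Sections 5.5 and 7.3 tie a new BAL to a suspected pulmonary infection, and section 10.1 counts infectious events. None lists the signs that make an event infectious. Section 7.4 ties samples to a change of antibiotic, not to signs at the sampled site. The gap remains.

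**3. Lung line against sections 7.2.1 and 7.3.** Section 7.2.1 uses persistence of the original organism in the BAL as a component of treatment failure. Section 7.3 requires a different organism for superinfection. Appendix XIII requires neither, so one BAL growing the index organism can contribute to failure and also meet the superinfection definition.

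**4. Size (illustration).** The protocol states no superinfection rate, colonisation rate or power for this objective, so there is no figure of its own to reproduce. Inputs:

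- n = 140 per arm, from the last row of the table in section 11.2 (350 pre-included, 280 included).
- Assumed true infection rates p of 30% (15 days) and 20% (8 days).
- Assumed share f of uninfected patients with a culture-only positive.
- Two-sided alpha 0.05.

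Observed rate = p + (1 − p)f. If f is the same in both arms, the observed difference is (0.30 − 0.20)(1 − f).

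Power = Φ[(d − 1.96·SE0)/SE1], where d is the observed difference, SE0 uses the pooled rate and SE1 the separate rates.

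| f, both arms | 15 days | 8 days | Difference (points) | Risk ratio | Power |
| --- | --- | --- | --- | --- | --- |
| 0 | 30.0% | 20.0% | 10.0 | 0.67 | 49% |
| 10% | 37.0% | 28.0% | 9.0 | 0.76 | 36% |
| 20% | 44.0% | 36.0% | 8.0 | 0.82 | 28% |

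Unequal f, same true rates:

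- f = 20% long, 10% short: 0.30 + 0.70 × 0.20 = 0.44 and 0.20 + 0.80 × 0.10 = 0.28. The difference is 16 points.
- f = 10% long, 20% short: 0.30 + 0.70 × 0.10 = 0.37 and 0.20 + 0.80 × 0.20 = 0.36. The difference is 1 point.

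A true 10-point difference can therefore be shrunk, nearly erased or inflated, depending on how culture-only positives fall between the arms.

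**The case against.** The strongest reply is that Appendix XIII is only the bacteriological confirmation of an event already suspected on clinical grounds. Sections 5.5, 7.3 and 10.1 support this: the protocol describes no surveillance BAL, and section 10.1 counts infectious events. This part stands. A reader might infer that patients with no sign of disease are counted as infected. For the lung the documents do not support that. What remains is that the signs making an event infectious are never stated, so the confirmation has nothing defined to confirm.

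A reader might also infer that one fever produces several counted infections. Section 7.4 does not ask for several sites to be cultured, no section sets the counting unit, and the word prevalence in section 10.1 fits counting by patient.

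The objective is worded for potentially fatal (section 3) or fatal (section 10.1) infections, which might seem to screen out trivial positives. Appendix XIII carries no severity condition, so that wording does no such work in the definition.

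Finally, the objective is secondary, it has no power target, and every rate used above is assumed. All of that is correct and limits the weight of the point.

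**Conclusion.** The point holds as a defect in the definition of a secondary outcome, and it should be corrected. Four of the six lines of Appendix XIII rest on culture alone, and the lung line disagrees with section 7.3. The section 10.1 comparison therefore mixes infection with colonisation or persistence of the first organism.

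It is tempting to say that the comparison is simply diluted. That follows only if false positives are equal in the two arms. The design is open, and section 2.2 itself raises the possibility of more colonisation with longer treatment, so the documents support an unknown direction of bias.

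The size is illustrative. It rests on assumed true rates of 20% and 30%, 140 per arm, and assumed false-positive shares of 10% to 20%. On those assumptions power falls from 49% to 36% or 28%, or a 10-point difference becomes 16 points or 1 point.

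A reader might also infer that the primary endpoint is affected, because sections 7.2.1 and 7.2.2 make exceptions for another documented infection. Those sections do not cite Appendix XIII, so the documents do not establish this.

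**What to change.** Reconcile Appendix XIII with sections 4, 7.3 and 10.1:

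- **Lung:** require an organism different from that of the index BAL, as section 7.3 does, plus new or worsening temperature, leucocytes or radiological score. Compare these with the days just before the event. The rise in section 4.2 is measured from the admission film, and every included patient has already met it, so reusing it would not identify a new infection.
- **Catheter, sinus and wound:** count as infection only a positive culture accompanied by new or worsening temperature or leucocytes, local signs, or the same organism in blood. Asking for change rather than an abnormal level avoids validating a colonised site in a patient still febrile from the first pneumonia.
- **Reporting:** show culture-only positives separately as colonisation, and analyse section 10.1 as patients with at least one superinfection.

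Cost: fewer events will be counted. Maximum temperature, leucocytes and radiological score are already on the daily sheet (Appendix VII), but local signs, character of secretions and minimum temperature are not, so a small addition to the form is needed. Local signs bring some investigator judgement into an open trial. Keeping the count under the present culture-only definitions as a supporting table shows how much that matters and loses no information.
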